### 5. OUTCOMES

#### 5.1 Primary outcome

##### 28-day all-cause mortality

Twenty-eight (28) day mortality is the most commonly used measure by scientific and regulatory authorities to assess efficacy of treatment of sepsis, and that will be the primary outcome of the study.

#### 5.2 Secondary outcomes

| Secondary outcomes                                 |                                                                                                                      |
|-----------------------------------------------------------|----------------------------------------------------------------------------------------------------------------------|
| ICU mortality,                                     | The proportion of patients who had died to ICU discharge                                                             |
| Hospital mortality                                 | The proportion of patients who had died to hospital discharge                                                        |
| Length of stay (LOS) in the ICU                    | The total duration of stay in the ICU for the first 28 days after randomization                                      |
| LOS in hospital                                    | The total duration of stay in the hospital for the first 28 days after randomization                                 |
| 28-day cumulative mechanical ventilation-free days | The total number of days a patient was alive and not on mechanical ventilation support from randomization to 28 days |
| 28-day ICU-free days                               | The number of days alive and free of ICU from randomization to 28 days                                               |
| The change in SOFA score on day 3                  | The change in SOFA score from baseline score measured at randomization to the score at Day 3                         |
| The change in SOFA score on day 6                  | The change in SOFA score from baseline score measured at randomization to the score at Day 6                         |

|                                                                                                |                                                                                                   |
|------------------------------------------------------------------------------------------------|---------------------------------------------------------------------------------------------------|
| The change in Acute Physiology and Chronic Health Evaluation (APACHE) II score on day 3 | The change in APACHE II score from baseline score measured at randomization to the score at Day 3 |
| The change in APACHE II score on day 6                                                  | The change in APACHE II score from baseline score measured at randomization to the score at Day 6 |

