## 4.3 Randomization

This study adopts a third-party interactive web response system (IWRS), which is implemented as competitive enrolment with a randomized block design. The random process is blinded to the investigators. Subjects are assigned to the treatment group and the placebo group at a 1:1 ratio.

When the screened subjects are eligible for recruitment, investigators at subsites log in to the IWRS and enter the subjects' basic information, including their screening numbers and initials, according to the system prompts. The IWRS randomly assigns the subjects SOFA scores (2-7 points vs. 8-13 points) as a stratification factor. The SSID (6 digits) and random number (4 digits) of each subject are unique and bound to each other.

After random numbers are generated, drug managers log in to the IWRS again for the allocation results and then provide this information to study nurses and dispense the investigational products to study nurses for instillation.

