## **8. STATISTICAL CONSIDERATIONS**

### **8.1 Power Calculation and Sample Size**

Based on the previous observational CHESS study conducted in China, a 28-day all-cause mortality rate of 24.3% in the placebo group was assumed in this trial. With a dropout rate of approximately 15%, a sample size of 1800 patients provided 80% power at the two-sided 0.05 significance level on an assumption of an absolute risk reduction of 6% in mortality.

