### **8.2 Analysis of Results**

A senior statistician at Dongzhimen Hospital will perform data analysis on an intention-to-treat basis. Summary statistics will be used to describe the clinical data and presented as mean  $\pm$  SD, or percentages as appropriate. Continuous variables will be compared using a two-sample t-test or Wilcoxon rank-sum test if data show serious deviations from a normal distribution. Categorical data or ordinal data will be compared using a Wilcoxon rank-sum test, chi-square test or Fisher's exact test, as appropriate. All tests will be two-sided. Statistical significance declared for probability values of 0.05 or less. Analysis of the outcome of excluded patients due to other trials etc. will be in accordance with the CONSORT guidelines.

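### ICU and hospital length of stay make no allowance for death, so an early death in the unit counts as a short stay and the comparison can point the wrong way

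*Protocol*

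**What the plan says.** Section 5.2 (Secondary outcomes) defines ICU length of stay as "The total duration of stay in the ICU for the first 28 days after randomization". Hospital length of stay is defined in parallel. Neither definition is limited to survivors, and neither says how a death is scored. Section 7.1 ends follow-up at death or day 28, whichever is first, so a stay that ends in death stops on the day of death.

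Section 8.2 (Analysis of Results) fixes the comparison: "Continuous variables will be compared using a two-sample t-test or Wilcoxon rank-sum test if data show serious deviations from a normal distribution". The analysis is by intention to treat.

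Two other outcomes in the section 5.2 table, ventilation-free days and ICU-free days, count only days on which the patient is alive. The two length-of-stay outcomes have no such term, and no outcome counts days alive and out of hospital.

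Section 8.1 gives the planning figures: "a 28-day all-cause mortality rate of 24.3% in the placebo group was assumed in this trial", and "an absolute risk reduction of 6% in mortality".

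**The concern.** A shorter stay is normally read as a better result. As defined here, a stay is short either because the patient recovered quickly or because the patient died quickly, and the t-test and Wilcoxon test treat the two alike. If the drug prevents early deaths, the saved patients swap a short stay ending in death for what may be a longer stay ending in discharge. Mean stay then rises on the better arm although nobody recovered more slowly. A harmful drug would produce the reverse.

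This trial is planned around a mortality difference, so the mechanism works through the very effect it is looking for. At stake is a report that sets a true mortality benefit beside an apparently longer stay, with a p-value, when the second result is only a by-product of the first.

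**Working it through.** **The plan's own figure.** Section 8.1 states that "a sample size of 1800 patients provided 80% power at the two-sided 0.05 significance level", with 15% dropout. For 24.3% against 18.3%, two-sided 0.05 and 80% power, the continuity-corrected formula gives 763 per arm, 1526 in total, and 1526 / 0.85 = 1796. Without the correction it gives 730 per arm, 1460 in total, and 1718 after dropout. Power at 765 per arm (1800 less 15%) is 81.8%. The 1800 is reproduced, and the point below does not touch it. The protocol gives no planning figure for length of stay.

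**Formula.** Allocation is 1:1 (section 4.3). Suppose the drug does nothing except prevent the planned deaths. Then 0.243 − 0.183 = 0.06 of treated patients, or 54 per 900, move from death to survival, and

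shift in mean stay (drug − placebo) = 0.06 × (mean stay if saved − mean stay if died).

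The sign depends only on whether saved patients stay longer than they would have lived.

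**Assumed timings (none is in the documents).** All deaths occur in the ICU. Time to death is exponential. The stay of saved patients is lognormal with log-scale SD 0.5. Other survivors have a median stay of 8 days (lognormal, SD 0.7), the same in both arms. All times are capped at day 28. For example, with a median time to death of 5 days the capped mean is 7.06 days. With a median saved stay of 14 days the capped mean is 15.21 days. The shift is 0.06 × (15.21 − 7.06) = +0.49 day.

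The last three columns come from 400 simulated trials of 900 per arm for each row. The last two give the share of trials with p < 0.05 and a longer mean stay on the drug.

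| Median time to death (days) | Median stay if saved (days) | Shift by formula (days) | Simulated shift (days) | Against drug, t-test | Against drug, Wilcoxon |
|---|---|---|---|---|---|
| 3 | 14 | +0.65 | +0.65 | 57% | 64% |
| 5 | 8 | +0.12 | +0.12 | 6.5% | 12% |
| 5 | 14 | +0.49 | +0.51 | 34% | 42% |
| 5 | 18 | +0.69 | +0.66 | 54% | 49% |
| 8 | 14 | +0.28 | +0.30 | 14% | 21% |
| 8 | 8 | −0.09 | −0.06 | 2% | 5% |
| 10 | 8 | −0.20 | −0.22 | 0% | 0.5% |

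A second set of assumptions has lognormal times, median death at day 5, a median survivor stay of 9 to 12 days, and saved patients staying as long as other survivors. It gives +0.25 to +0.44 day, with Wilcoxon p ≤ 0.05 in 19% to 30% of trials, mostly against the drug. Moving the median death to day 7, with a 9-day survivor median, reduces the shift to about +0.1 day.

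**Comparison with ICU-free days.** In the simulated data of the table, ICU-free days (zero for a death in the ICU) favoured the drug in every row, by +0.60 to +1.15 days. In the row with medians of 5 and 14 days, ICU stay is about 0.5 day longer on the drug while ICU-free days are 0.76 day better. Two outcomes from one table would then disagree about the same patients.

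Hospital stay was not simulated. The same formula applies, with hospital days in place of ICU days.

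**The case against.** **ICU stay already has a companion.** ICU-free days, ICU mortality and hospital mortality are in the same table. A patient who dies without leaving the ICU has no ICU-free days, so a reader of both results would see the conflict. This stands for ICU stay and reduces the harm there. It does not cover hospital stay.

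**The outcomes are secondary.** No decision in the protocol hangs on them, and the primary outcome is untouched. This stands, and it makes the change an inexpensive improvement, not a threat to the trial.

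**Total days measure bed use.** As a description of resource use, counting a death as the end of a stay is legitimate. This stands too, and is a reason to keep the figures as description. It does not justify a test that will be read as evidence about recovery.

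**The analysis plan could settle it.** An analysis plan not shown here may add a death-aware analysis. But for length of stay the protocol itself fixes both the definition and the test, and a plan that follows them reproduces the problem.

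**Stronger readings that a reader might infer.**
- That length of stay must count against an effective drug. It need not: the last two rows of the table have the opposite sign.
- That an early death scores the best possible value. It does not: a live discharge on day 1 is shorter than a death on day 2.
- That the four SOFA and APACHE II change outcomes share the defect. The protocol defines, for example, "The change in SOFA score from baseline score measured at randomization to the score at Day 6" and is silent on patients who die first. Handling of scores missing through death is commonly left to the analysis plan, so this silence is not an error. The effect also looks small for SOFA. Assume 20% to 50% of deaths fall by day 6, so that 4.9% to 12.1% of placebo and 3.7% to 9.1% of treated patients have no score. Assume also a change of −3 in other patients and 0 to +2 in those saved. The treated mean is then −2.96 to −2.83 against −3.00, a shift of 0.04 to 0.17 point.

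**Conclusion.** The point holds for the two length-of-stay outcomes and is limited to them. As defined and tested, they mix quick recovery with quick death. At the planned mortality difference, prevented deaths alone shift mean ICU stay by about +0.1 to +0.7 day against a life-saving drug when deaths are early (median 3 to 5 days). The shift is about 0 to −0.2 day when deaths are late (median 8 to 10 days) and saved patients leave early. With late deaths but long stays in those saved, it is still positive (about +0.3 day). The chance of a nominally significant result against the drug runs from near zero to over half.

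The formula and the 6 points follow from the protocol. The timings, the distributions, the placing of all deaths in the ICU and the absence of any effect on other survivors are assumptions, so neither size nor direction can be predicted for this trial. What does follow is that a difference in stay cannot be interpreted as benefit or harm on recovery. The gap is greatest for hospital stay, which has no death-aware counterpart.

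**What to change.** In section 5.2, define both outcomes as time from randomization to discharge alive, from the ICU and from hospital respectively, within 28 days, with death as a competing event. In section 8.2, state that they are compared by cumulative incidence of live discharge by arm, with a matching test such as Gray's in place of the t-test or Wilcoxon test. Keep days of stay as a description by survival status, without a test.

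The dates and vital status needed are already required for the existing mortality and stay outcomes, so nothing new is collected and the sample size does not change. There are two small costs. The new outcome partly reflects mortality and so overlaps with the primary, which is why the survivors' stay should be shown beside it. Also, a total of days can add up several stays whereas a time to discharge cannot, so one line is needed on how readmission within 28 days is treated.

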### 5.3 Safety outcomes

- 1) Incidence of serious adverse events (SAEs)
- 2) Incidence of adverse events (AEs)

## 6. ETHICS AND DISSEMINATION

### 6.1 Guiding Principles

This study is to be performed in accordance with the ethical principles of the Declaration of Helsinki (June 1964 and amended 1975, 1983, 1989, 1996, 2000, 2008, 2013 and Note of Clarification 2002 and 2004), China GCP Notes for Guidance on Good Clinical Practice (GCP).

### 6.2 Ethical Considerations

Ethical review procedure: All subsites engaged in this study must be reviewed and approved by the ethics committee of the hospital before study initiation. The amendment of the study protocol and informed consent form should be submitted to the ethics committee for re-review and re-approval;

Ethics committee review of the sponsor's organization: Prior to study initiation, the principal investigator should submit the investigator's brochure, study protocol, informed consent form, CRF, and qualifications and resumes of the investigators, and other major study materials to the ethics committee of the study sponsor's organization for review and approval;

Ethics committee review of the subsite organization: The principal investigator of each subsite should submit the approval letter issued by ethics committee of the sponsor's organization, the investigator's brochure, study protocol, informed consent form, CRF, qualifications and resumes of the principal investigator from the subsite, and other study data to the ethics committee of the hospital for review and approval;

When reviewing and approving study documents, the ethics committee must confirm the study title and indicate the version number, version date and review date of the reviewed study documents.

### 6.3 Informed Consent Form

The investigator must inform the subject or his/her legal representative of the information about the study in both oral and written ways. The subjects or their legal representatives have the right to know the detailed information about this study.

The informed consent form (ICF) must be reviewed and approved by the ethics committee. If necessary, the investigator is responsible for explaining the contents of the ICF to the subject in a manner that the subject can understand. The subject or his/her legal representative should have sufficient time to read and understand the ICF before signing it.

The ICF must be signed and dated by the subject or his/her legal representative. The signed ICF should be kept separately by the investigator and the subject, and the investigator should keep the original copy on file for monitoring and audit.

### 6.4 Liability Insurance for Drug Clinical Trials

To provide better protection for the rights and interests of subjects, all subjects will be insured with "Ping An Clinical Trial Liability Insurance" before study initiation. A copy of the insurance certificate will be submitted to the ethics committee of each subsite for filing.

### 6.5 Privacy Protection of Subjects

The investigator takes the responsibility to maintain the anonymity of subjects and keep documents showing the identity of subjects strictly confidential. In CRFs or other study documents, subjects can only be identified with codes. The investigator must properly maintain a screening form that records the subject code, name, and home address.

### 6.6 Dissemination Policy

A writing committee will be formed to review and publish the data from the study. This committee will consist of the Steering Committee and a subset of investigators. The writing committee will write/review all drafts of abstracts and full-length manuscripts and will choose the appropriate journal (for manuscripts) or meeting (for abstracts) for submission.

The EXIT-SEP Steering Committee commits that when the study is completed, the data from this study will be published, regardless of the outcome of the study.

All information concerning the EXIT-SEP trial supplied to the investigators by the Steering Committee and not previously published is considered confidential and shall remain the sole property of the EXIT-SEP Steering Committee. The investigator agrees to use this information only in accomplishing the study and will not use it or the data generated from the study for other purposes without first obtaining written authorization from the EXIT-SEP Steering Committee.

## **7. DATA MANAGEMENT**

### **7.1 Data Collection Methods**

All data will be collected by trained staff at each study site using a case report form (CRF) worksheet developed by the coordinating centre. Data will then be entered into the web database (electronic case report form [eCRF]). Randomized patients will be followed up to death or 28 days post-randomization whichever occurs first. Study day 0 commences on randomization and concludes at the expiry of the calendar day. Data collection will be restricted primarily to those variables necessary to define clinical patient characteristics including: baseline demographics, primary diagnoses, physiological parameters, diagnostic interventions, therapeutic interventions and documentation of deaths and other SAEs.

### **7.2 Data Collection Methods**

CRF design: The data management organization will draft the CRF and submit it to the principal investigator for review and approval.

Database design: The data management organization will be responsible for designing the electronic database and developing the procedure for data logic verification per the study protocol. The data management organization shall test the database with simulated data or real CRF data.

Study data input: The study data input is the responsibility of the investigator. To ensure the accuracy of the data, the investigator needs to fill in the paper copy of the CRF carefully and enter its content into the electronic CRF. Problems found in the

entry process should be recorded and reported to the CRA and data management organization in a timely manner to take measures promptly.

#### Data verification

If an error occurs during the data entry process, the logic verification programme will mark the erroneous data entered in red, prompting the person inputting the data to make corresponding modifications.

The CRA is responsible for verifying the consistency of the paper CRF and electronic CRF, monitoring the quality of entries and analysing and handling existing problems.

Database lock: The principal investigator of all subsites will sign on the completed data and confirm it. After CRA verification, they will sign and confirm it. Once all the signed documents meet the requirements of the study protocol and the blinded review meeting is held, the data management organization will lock the database (no modification can be performed after database lock) and export clean data after the database is locked. Problems found after the data are locked will be modified in the statistical analysis programme after confirmation. All errors and modifications should be recorded and properly maintained.

### 7.3 Data Quality and Monitoring

Several procedures to ensure data quality and protocol standardization will help to minimize bias and to optimize data quality. The study will be monitored by quality control reviews of protocol compliance, data queries, safety reporting and protocol deviations. On-site monitoring will only be performed on a case by case basis if quality control issues are flagged by electronic review of data Medical records, any other relevant source documents and the site investigator files must be made available to the monitoring representative for these monitoring visits during the study and at the completion of the study as needed.

### 7.4 Protocol Deviations

A protocol deviation is an unanticipated or unintentional departure from the expected conduct of an approved study that is not consistent with the current research protocol or consent document. A protocol deviation may be an omission, addition or change in any procedure described in the protocol. Given that the investigator is responsible for patient

safety and care he/she may implement a deviation from, or a change of the protocol to eliminate an immediate hazard to trial patients without prior Human Research Ethics Committee approval. The implemented deviation or change must be reported in a protocol deviation form. The deviation must be reported via the study website by the principal investigator. A summary of protocol deviations will be reported to the coordinating Human Research Ethics Committee; a serious breach will be reported ASAP.

## **8. STATISTICAL CONSIDERATIONS**

### **8.1 Power Calculation and Sample Size**

Based on the previous observational CHESS study conducted in China, a 28-day all-cause mortality rate of 24.3% in the placebo group was assumed in this trial. With a dropout rate of approximately 15%, a sample size of 1800 patients provided 80% power at the two-sided 0.05 significance level on an assumption of an absolute risk reduction of 6% in mortality.

### **8.2 Analysis of Results**

A senior statistician at Dongzhimen Hospital will perform data analysis on an intention-to-treat basis. Summary statistics will be used to describe the clinical data and presented as mean  $\pm$  SD, or percentages as appropriate. Continuous variables will be compared using a two-sample t-test or Wilcoxon rank-sum test if data show serious deviations from a normal distribution. Categorical data or ordinal data will be compared using a Wilcoxon rank-sum test, chi-square test or Fisher's exact test, as appropriate. All tests will be two-sided. Statistical significance declared for probability values of 0.05 or less. Analysis of the outcome of excluded patients due to other trials etc. will be in accordance with the CONSORT guidelines.

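### Section 8.2 tests the four SOFA and APACHE II change scores without the baseline score or the SOFA randomisation stratum, which loses precision at no saving

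*Protocol*

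**What the plan says.** The table in section 5.2 defines four outcomes as changes from baseline:

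- SOFA, day 3: "The change in SOFA score from baseline score measured at randomization to the score at Day 3"
- SOFA, day 6: "The change in SOFA score from baseline score measured at randomization to the score at Day 6"
- APACHE II, day 3: "The change in APACHE II score from baseline score measured at randomization to the score at Day 3"
- APACHE II, day 6: "The change in APACHE II score from baseline score measured at randomization to the score at Day 6"

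Section 4.3 describes 1:1 allocation with "SOFA scores (2-7 points vs. 8-13 points) as a stratification factor". The synopsis places randomisation directly after the baseline SOFA score, so that score and its stratum are known for every randomised patient.

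Section 8.2 gives one rule for all continuous outcomes: "Continuous variables will be compared using a two-sample t-test or Wilcoxon rank-sum test if data show serious deviations" from normality. It names no covariate and no stratified test, and does not refer to a later plan for the method.

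**The concern.** A comparison of raw changes fixes the coefficient of the baseline score at 1. When the correlation between baseline and follow-up is well below 1, that over-corrects: patients who start worse tend to improve more whatever they receive, and this variation stays in the error term. ANCOVA estimates the coefficient instead.

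A second loss comes from the design. Randomisation balances the arms on SOFA stratum, but a two-sample test that ignores the stratum computes its standard error as if they had not been balanced.

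At stake is the precision of four organ-function outcomes that would be read alongside the mortality result.

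**Working it through.** **The protocol's own figure.** The only sample-size figure is for mortality. With 24.3% vs 18.3%, two-sided 0.05, 80% power and a continuity correction, the requirement is 763 per arm. Then 763/0.85 = 898 per arm, or 1796 in total, against the stated 1800. It reproduces, and nothing below changes it. After the assumed 15% dropout, 900 × 0.85 = 765 per arm remain.

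**Inputs not in the protocol (assumed).** rho is the correlation between baseline and follow-up score, taken as 0.3 to 0.7. k is follow-up SD divided by baseline SD, taken as 0.8 to 2.0.

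**Step 1: residual variance.** With baseline variance s²:

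- raw change: s²(1 + k² − 2·rho·k)
- ANCOVA: s²k²(1 − rho²)
- proportional saving: (1 − rho·k)² / (1 + k² − 2·rho·k)

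The saving is a square over a variance, so in large samples it cannot be negative. At k = 1 it reduces to (1 − rho)/2.

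| k | rho 0.3 | rho 0.5 | rho 0.7 |
|---|---|---|---|
| 0.8 | 50% | 43% | 37% |
| 1.0 | 35% | 25% | 15% |
| 1.25 | 22% | 11% | 2% |
| 1.5 | 13% | 4% | 0.2% |
| 2.0 | 4% | 0% | 7% |

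At k = 1 under simple randomisation, an effect with 80% power on the raw change has about 94%, 90% or 86% power with ANCOVA (rho 0.3, 0.5, 0.7).

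**Step 2: bias and chance imbalance.** Under simple randomisation with 765 per arm, the between-arm difference in mean baseline has SE √(2/765) = 0.051 baseline SD, so 95% of trials lie within 1.96 × 0.051 = 0.10 SD. At k = 1 a share (1 − rho) passes into the raw-change contrast: at most about 0.07 SD at rho 0.3 and 0.03 SD at rho 0.7. Averaged over randomisations the shift is zero.

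**Step 3: SOFA, allowing for stratification.** Assume baseline SOFA is roughly normal (mean 7, SD 3), cut to the eligible range 2-13. The share of variance left within the two strata is then w = 0.32, so about 68% of the variance behind chance imbalance is removed. (With mean 6 and SD 2.5, w = 0.39, so about 61% is removed.) With k = 1 and w = 0.32:

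- true gain from ANCOVA: (1 − rho)w / [(1 − rho)w + 1 + rho]
- true variance of the raw-change contrast over the variance the t-test assumes: [(1 − rho)w + 1 + rho] / 2

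| rho | true gain | variance ratio | type I error of t-test |
|---|---|---|---|
| 0.3 | 0.224/1.524 = 15% | 0.762 | 2.5% |
| 0.5 | 0.160/1.660 = 10% | 0.830 | 3.1% |
| 0.7 | 0.096/1.796 = 5% | 0.898 | 3.9% |

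The last column is the two-sided normal tail beyond 1.96/√(variance ratio).

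A simulation under the same assumptions (2000 runs, 1530 patients, allocation balanced within strata, no treatment effect, ANCOVA on baseline) agrees. The gains were 14%, 10% and 5%, and the t-test's type I error was 2.6%, 3.0% and 3.7%. The mean raw-change difference was within 0.004 SOFA points of zero.

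**Step 4: APACHE II.** It is not a stratification factor, so Step 1 applies more nearly in full. It is reduced only as far as APACHE II correlates with SOFA stratum, which the protocol does not quantify.

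**The case against.** **Not bias.** A reader might infer that unadjusted change scores bias the treatment contrast. They do not. Under 1:1 randomisation the contrast is unbiased, and a chance imbalance is sampling variation that the standard error already counts. For SOFA the error of the planned test is on the safe side: power is lost, and no excess of false positives arises. This objection stands in full.

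**Not a known 15-35%.** That range needs both rho of 0.3-0.7 and equal SDs, and the protocol supplies neither. Eligibility restricts baseline SOFA to 2-13 and excludes liver or kidney components of 3 or more, while follow-up scores have no such limit. The follow-up SD may therefore exceed the baseline SD, and the gain could be near zero. This also stands.

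**Left to the SAP.** Covariates for secondary outcomes are often fixed there, and the SAP is not at hand. But 8.2 is not silent: it names unadjusted tests, and an adjusted model in the SAP would depart from it. This objection does not remove the point.

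**The switch between t-test and Wilcoxon.** One might call the data-dependent choice an error. It is common convention and carries no weight here. If the scores are treated as ordinal and analysed by ranks, the variance ratios above do not apply directly.

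**Deaths.** ANCOVA does not settle how patients who die before day 3 or day 6 are handled, and they reduce the analysed number below 765 per arm. That is true, but it applies equally to the planned tests.

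**Conclusion.** The point holds as a free improvement. Section 8.2 fixes an analysis of four secondary outcomes that ignores a baseline the trial collects and a stratum it randomises on.

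The size is uncertain because it rests on an assumed correlation and SD ratio: about 0-50% of residual variance over the range examined. For SOFA the real precision gain is modest, roughly 5-15% with equal SDs and the assumed baseline distribution; the more definite defect there is a conservative test. For APACHE II the gain can be larger. The mortality analysis and its sample size are untouched.

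**What to change.** Add one sentence to section 8.2: SOFA and APACHE II at days 3 and 6 will be analysed by ANCOVA with treatment, the baseline value of the same score and the randomisation SOFA stratum (2-7 vs 8-13), reporting the adjusted mean difference with its 95% CI. The rank-sum test may stay as a sensitivity analysis.

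With baseline in the model, analysing the follow-up score or the change gives the same treatment estimate, so the definitions in section 5.2 can stand. The change needs no new data and no more patients. It should be fixed before unblinding and matched in any SAP.

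### Randomisation is stratified by SOFA, but the test the protocol assigns to 28-day mortality is not, which gives away a little power that could be had for free

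*Protocol*

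**What the plan says.** - **Design (protocol, 4.3 Randomization).** Allocation is "implemented as competitive enrolment with a randomized block design", at 1:1. On stratification the section says "The IWRS randomly assigns the subjects SOFA scores (2-7 points vs. 8-13 points) as a stratification factor". The sentence is awkward, but the evident meaning is that allocation is stratified by SOFA band. No other stratification factor is named and no block size is given.
- **Outcome (5.1 Primary outcome).** Death from any cause by day 28, a yes/no outcome.
- **Analysis (8.2 Analysis of Results).** One general paragraph covers all outcomes: "Categorical data or ordinal data will be compared using a Wilcoxon rank-sum test, chi-square test", with Fisher's exact test as the third option. Analysis is by intention to treat, two-sided, at 0.05. The paragraph does not name the mortality test separately. It mentions neither the SOFA stratum nor any adjustment, and it specifies no confidence interval.
- **Sample size (8.1 Power Calculation and Sample Size).** "a 28-day all-cause mortality rate of 24.3% in the placebo group was assumed in this trial", with "an assumption of an absolute risk reduction of 6% in mortality"; "a sample size of 1800 patients provided 80% power at the two-sided 0.05 significance level", allowing about 15% dropout.

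**The concern.** Blocked randomisation within SOFA strata keeps the arms balanced on SOFA. Differences in mortality between the strata then contribute almost nothing to the true sampling variance of the treatment difference. An ordinary chi-square test still counts those differences as noise. If patients with SOFA 8-13 die more often than those with SOFA 2-7, the test's standard error is larger than the true one. Its real type I error then falls below 5%, and it detects a real effect less often than the design allows.

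The protocol gives reason to expect SOFA to be prognostic. It is the only stratification factor, and the Introduction links organ dysfunction to prognosis under Sepsis-3. At stake is some efficiency in the single confirmatory comparison. Validity is not at stake.

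**Working it through.** **1. The protocol's own figure.** Inputs from 8.1: p0 = 0.243, p1 = 0.243 − 0.06 = 0.183, mean 0.213, two-sided alpha 0.05, power 80%, dropout 15%.

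- Simple formula: n = [1.96·√(2·0.213·0.787) + 0.842·√(0.243·0.757 + 0.183·0.817)]² / 0.06² = 730 per arm. Total 1460 / 0.85 = 1718.
- With continuity correction: (n/4)·[1 + √(1 + 4/(n·0.06))]² = 763 per arm. Total 1526 / 0.85 = 1796, which matches the stated 1800.
- 1800 × 0.85 = 1530 evaluable, or 765 per arm. Power of the uncorrected pooled two-proportion test at that size is 81.8%.

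The sample size reproduces as a plain comparison of two proportions with no allowance for strata.

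**2. Assumptions that the protocol does not supply.** 40% of patients are in SOFA 8-13. Placebo mortality in SOFA 2-7 vs 8-13 is 18% vs 34%, 16% vs 37%, or 13% vs 41%, so the overall placebo rate is 24.4%, 24.4% or 24.2%. The risk ratio is 0.183/0.243 = 0.753 in both strata. The arms are balanced within strata.

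**3. Formulas.** With P0 and P1 the overall risks and d = P0 − P1:

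- Variance used by the unstratified test: V_u = P0(1−P0) + P1(1−P1).
- True variance, within strata: V_s = sum over strata of share × [p0(1−p0) + p1(1−p1)].
- SE = √(V/765).
- Power, unstratified: Φ[(d − 1.96·SE_u)/SE_s]. Power, stratified: Φ[d/SE_s − 1.96].
- True alpha, unstratified: 2·[1 − Φ(1.96·√(V_u/V_s))], using the same variance ratio under the null as an approximation.
- Patient equivalent: the n per arm at which the unstratified test reaches the stratified test's power at 765, from √n = (1.96·√V_u + z·√V_s)/d, with z = d/SE_s − 1.96.

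**4. Middle case in full (16% vs 37%).**

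- Treated risks 0.1205 and 0.2786; P0 = 0.2440, P1 = 0.1838, d = 0.0602.
- V_u = 0.244·0.756 + 0.1838·0.8162 = 0.3345.
- V_s = 0.6·(0.1344 + 0.1060) + 0.4·(0.2331 + 0.2010) = 0.3179. Ratio 0.95.
- SE_u = 0.02091, SE_s = 0.02038.
- Power 82.8% unstratified, 84.0% stratified. True alpha 0.044.
- Matching n = 792 per arm, so 2 × (792 − 765) = 54 more evaluable patients.

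**5. All cases** (gains from unrounded values):

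| Placebo mortality, SOFA 2-7 / 8-13 | V_s/V_u | True alpha | Power, unstratified | Power, stratified | Gain (points) | Matching n per arm | Extra evaluable patients |
|---|---|---|---|---|---|---|---|
| 18% / 34% | 0.97 | 0.047 | 82.5% | 83.2% | 0.7 | 781 | 32 |
| 16% / 37% | 0.95 | 0.044 | 82.8% | 84.0% | 1.3 | 792 | 54 |
| 13% / 41% | 0.91 | 0.040 | 82.9% | 85.1% | 2.3 | 814 | 98 |
| 24.3% / 24.3% | 1.00 | 0.050 | 82.0% | 82.0% | 0 | 765 | 0 |

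The last row shows 82.0% where step 1 gives 81.8% because this table uses the unpooled variance.

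**6. Wider check.** This used a common odds ratio and a pooled standard error, 20-50% of patients in SOFA 8-13, and high-to-low mortality ratios from 1.5 to 4, with 40,000 simulated trials per scenario. The power loss is 0.2 to 2.5 points for ratios of 1.5 to 3, and up to 4.3 points at a ratio of 4. True alpha runs from 0.049 down to 0.031. Unstratified power is at or above 80% in every scenario.

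**The case against.** **This belongs in the SAP.** Section 8.2 is generic, never uses the word unstratified, and a Cochran-Mantel-Haenszel test is itself a kind of chi-square test. The SAP was not available and may specify a stratified analysis. This stands in part: that the primary test is unstratified is the natural reading, but it is an inference. The point survives because 8.2 does choose tests, and those it lists make no use of the factor in 4.3. A better method is available at no cost.

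**The effect is small and its size is assumed.** This stands. Only the direction is secure, and it depends on SOFA being prognostic.

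A reader might also infer more than the protocol supports:

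- *That the test is invalid or the trial underpowered.* The error is on the conservative side, there is no bias, and power stays above 80%.
- *That reported confidence intervals will be too wide.* Section 8.2 specifies none.
- *That three open tests leave real room to choose after the fact.* For a binary outcome the rank-sum test is in large samples the chi-square test, and Fisher's test is ordinarily kept for sparse tables. About 326 deaths are expected (765 × (0.243 + 0.183)), so the choice carries little practical weight.
- *That stratifying saves about 80 or 150 patients.* That comes from applying the variance ratio to the sample, 1530 × (1/0.95 − 1) or 1530 × (1/0.91 − 1). It ignores that the unstratified test already benefits from the smaller true variance. Matching power gives 54 and 98.

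**Conclusion.** The point holds as a free improvement. On its natural reading, 8.2 tests 28-day mortality without the stratum that 4.3 randomises by. If SOFA predicts death, this makes the test mildly conservative and costs about 0.7 to 2.3 points of power at 765 per arm in the three cases worked, with true alpha between about 0.047 and 0.040. These sizes rest on an assumed 40% share in SOFA 8-13, assumed stratum mortalities, a common risk ratio and balance within strata. With no prognostic effect of SOFA the two analyses have the same power. The validity of the trial and its sample size are not in question.

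**What to change.** In 8.2, name the primary test of 28-day mortality: a Cochran-Mantel-Haenszel test stratified by the SOFA stratum used at randomisation (2-7, 8-13), reported with the Mantel-Haenszel risk difference and risk ratio and their 95% confidence intervals. Use the same method for ICU and hospital mortality. Keep the unstratified chi-square as a sensitivity analysis, and carry the same wording into the SAP.

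The cost is a sentence or two of text. The stratum is already held in the randomisation system, so no new data and no additional patients are needed, and the sample size can stay at 1800.
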